#### Cardiopulmonary exercise test

Patients will undergo cardiopulmonary exercise testing (CPET) on a treadmill using an incremental RAMP protocol based on American Thoracic Society guidelines [34]. A RAMP slope, based on gender, age, and estimated physical fitness of the subject will be set to obtain a test of approximately 10 min duration. Subjects will wear a tight facemask to permit continuous measurements of ventilation, oxygen consumption (VO_2_), and carbon dioxide production (VCO_2_) in expired gas, from which estimates of peak oxygen consumption (peak VO_2_) and anaerobic threshold (AT) can be obtained using a V-slope method [35].

#### Transthoracic echocardiography

Transthoracic echocardiography will be performed by experienced echocardiographers accredited through the British Society of Echocardiography (BSE). LV and right ventricular (RV) dimensions, atrial dimensions, systolic and diastolic function will be assessed according to the requirements for the performance of a standard transthoracic echocardiogram according to BSE guidelines [36]. Estimated pulmonary artery systolic pressure will be derived from the regurgitant jet of tricuspid regurgitation calculated by the modified Bernoulli equation and allowance made for right atrial pressure. Myocardial tissue velocity and deformation will be assessed using 2D speckle tracking [37].

#### Stress echocardiography

Stress echocardiography will be carried out at the baseline visit according to previously described methods [38], but in brief, semi-supine bicycle ergometry will be performed initially at workloads of 20-25 W for 2 min, then increased in steps of 15-30 W every 2 min as decided according to the physical fitness and symptom status of the patient. During each 2-min interval, MR quantification and estimations of LV filling pressure and pulmonary artery pressure are performed (Epic, Phillips). LV size and systolic function are assessed at baseline and peak exercise. Global longitudinal strain will be derived from the apical 2–3- and 4-chamber views via speckle tracking at baseline and peak exercise. The quantification of MR will be carried out using the integration of quantitative and qualitative approaches [39]; ‘quantitatively’ by subtracting the stroke volume across the left ventricular outflow tract (LVOT) from the stroke volume across the MV annulus, or the flow convergence method by proximal isovelocity surface area; and ‘qualitatively’ by visual assessment of the colour flow jet area and flow convergence zone.

#### Electrocardiogram

A standard 12 lead electrocardiogram (ECG) will be performed for the assessment of baseline heart rate, rhythm, and QRS morphology, followed by signal-averaged ECG (SA-ECG) for the assessment of ventricular late potentials in those with sinus rhythm. SA-ECG will be performed by averaging 250 beats using a MAC® 5500 system (GE Healthcare, Illinois, U.S.A.) at a filter setting of 40-250 Hz and aiming for a noise level of <0.3 μV.

#### 24-h Holter monitoring

3-channel 24-h Holter ECG recordings will be carried out using Lifecard CF monitors (Spacelabs Healthcare, Snoqualmie, U.S.A.). Holter data will be independently analysed at University Hospital Birmingham using Pathfinder SL software (Spacelabs Healthcare, Snoqualmie, U.S.A.). Supra-ventricular and ventricular ectopic burden, as well as the type and frequency of arrhythmic events, will be recorded. Time-domain analyses will be recorded from automated measurements of heart rate variability (HRV). Maximum, mean and minimum QT and QTc duration from automated software assisted analyses will be recorded according to previously established methodology [40].

#### Laboratory tests and biomarkers

All patients will undergo routine blood tests for full blood count, urea and electrolytes, liver function tests, C reactive protein, N-terminal pro-B natriuretic peptide, and high-sensitivity troponin T (lower limit of detection 5 ng/L, Roche) at the baseline and follow-up visits. Blood tests will be carried out at the Clinical Biochemical services at University Hospital Birmingham.

At initial visit, serum samples will also be stored for the measurement of collagen turnover markers including the amino terminal of type I and type III procollagen, circulating levels of matrix metalloproteinase-1 and tissue inhibitor of metalloproteinase-1 using commercially available ELISA assays.

#### Histology

Intraoperative myocardial biopsies (Tru-Cut biopsy needle) will be taken from the LV septum, anterior and posterior LV free wall. Samples will be fixed immediately in 10% buffered formalin, embedded in paraffin, and sections will be stained with Elastic Van Gieson (EHVG) for assessment of myocardial fibrosis. The EHVG stains fibrous tissue pink, elastic tissue purple and the muscle brown. Digital images (300dpi x 300dpi resolution, image size 1280 × 960 pixels) of the whole EHVG stained slide at 4× objective magnification (12 per biopsy) will be taken and analysed using Image J software (version 1.50i, National Institutes of Health, Bethesda, USA) by a specialist cardiac histopathologist, blinded to the imaging findings. The area of the tissue and the area of fibrosis will be determined by manually drawing around the outline of the tissue, and each area of pink/purple fibrosis using the surface pen on a surface book tablet. Measurements will be given in pixels and the percent fibrosis can be calculated.

#### Patient reported outcome symptom status

Subjects will be asked to provide data at entry and at 9 months post-surgery or post-first surveillance using a self-completion questionnaire (SF-36 and Minnesota Living with Heart Failure (MLWHF)) to eliminate any observer bias. The SF-36 has established validity in measurement of functional status in patients undergoing MV repair [41] but the MLWHF and SF-36 emotional score will also be collected for exploratory analysis to inform larger studies.

### Subject withdrawal

Patients may withdraw consent from the study at any time. If the withdrawal is initiated by a healthcare professional, full details for the reason for withdrawal is recorded on the case report forms. In all other cases, a simple statement reflecting patient preference is noted.

### Planned statistical analysis

All analyses will be carried out on an intention to treat basis. For all tests, summary statistics will be reported and 95% confidence intervals will be constructed where appropriate. A *P* value of <0.05 will be considered statistically significant without adjustment for multiple testing. Analyses will also be performed according to the following subgroups: severity of MR, degree of ventricular function as measured with above- and below-median global myocardial strain, presence or absence of subjective symptoms, and peak VO_2_ of ≥80% or <80% on CPET.

### Power calculation

Applying in-house pilot data and informed by previous CMR studies [42], we expect the standard deviation of LV end-systolic volume indexed to body surface area (ESVi) will be 12 ml/m^2^. A survival advantage has previously been shown with a 7 ml/m^2^ difference in ESVi from pre- to post-surgery in patients with asymptomatic MR [9]. This change has been selected as a clinically-significant difference for the study; hence it is powered on a comparison of the change in ESVi between two groups: those above and below median ECV. An independent samples t-test with 48 patients per group (96 total) and a within-group standard deviation of 12 ml/m^2^ yield a minimum detectable difference of 7 ml/m^2^ at 80% power, with alpha = 0.05. We therefore plan to recruit 115 subjects allowing for a 15% drop-out rate.

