## Abstract

**Background:**

The optimal management of chronic severe primary degenerative mitral regurgitation (MR) is to repair the valve but identification of the optimal timing of surgery remains challenging. Current guidelines suggest ‘watchful waiting’ until the onset of symptoms or left ventricular (LV) dysfunction but these have been challenged as promoting ‘rescue surgery’. Better predictors are required to inform decision-making in relation to the necessity and timing of surgery. Chronic volume overload is a stimulus for adverse adaptive LV remodelling. Subclinical reduction in LV strain before mitral repair predicts a fall in LV ejection fraction following surgery and is thought to reflect the development of myocardial fibrosis in response to chronic volume overload. Myocardial fibrosis can be detected non-invasively using cardiac magnetic resonance (CMR) imaging techniques as an expansion of the extracellular volume (ECV).

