Therefore, this study aims to assess whether left ventricular fibrosis as measured through CMR impacts upon patient outcomes including ventricular recovery following surgery, post-operative complications and symptomatic improvement. The primary endpoint of this study is the reduction in end-systolic volume index on CMR (as a measure of reverse LV remodelling) at 9 months following surgery, comparing those with ECV measured pre-operatively above and below the median. The reduction in left ventricular end-systolic volume index (LVESVi) is a commonly measured outcome parameter for the quantification of reverse left ventricular remodelling in MR [9, 30]. Secondary end-points (Table 2) assess the difference in exercise performance, symptom status, post-operative recovery and ventricular contractility (measured by LVEF and myocardial strain) between patients with an above and below-median ECV before and 9 months after MV surgery.

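### The only analysis described for the primary comparison is a t-test on raw change in ESVi between observed ECV groups; without pre-operative ESVi as a covariate it may mask an adverse ECV effect

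*Protocol article*

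**What the plan says.** The last part of the Background sets the primary endpoint as the reduction in ESVi on CMR "at 9 months following surgery, comparing those with ECV measured pre-operatively above and below the median". The Abstract gives the expected direction: a smaller reduction when ECV is above the median. Table 2 repeats change in ESVi as the primary endpoint.

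The Power calculation states that "it is powered on a comparison of the change in ESVi between two groups: those above and below median ECV". It sizes that comparison with "An independent samples t-test with 48 patients per group (96 total", a "within-group standard deviation of 12 ml/m^2" and a "minimum detectable difference of 7 ml/m^2^ at 80% power, with alpha = 0.05".

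Planned statistical analysis names no test or model for the primary endpoint and no covariate. Its one remark on adjustment concerns multiple testing. MR severity, strain, symptoms and peak VO2 are listed as subgroups. Pre-operative ESVi is neither a covariate nor a subgroup.

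**The concern.** ECV is measured, not allocated, so nothing balances its two halves on starting volume. Pre-operative ESVi is one of the two terms in the change score, so an imbalance in it can enter the contrast directly.

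The article's own theory makes an imbalance plausible. The Abstract says that reduced strain "is thought to reflect the development of myocardial fibrosis in response to chronic volume overload", and the Background reports that fibrosis in the pilot correlated with strain and exercise capacity. If patients with more overload have both higher ECV and larger ventricles, and larger ventricles have further to fall after repair, the high-ECV half gains extra reduction unrelated to ECV. That works against the stated hypothesis.

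At stake is the purpose given in the Discussion: a marker to inform the timing of surgery whose value is that it does not depend on chamber volume. Showing this calls for the ECV difference at a given starting volume, which the raw contrast does not isolate.

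**Working it through.** **Inputs from the Power calculation:** 48 per group, SD 12 ml/m², difference 7 ml/m², 80% power, alpha 0.05.

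**Assumptions (not in the documents):**
- r, the correlation of ECV with pre-operative ESVi, is varied.
- ECV and pre-operative ESVi are bivariate normal.
- s, the slope of the reduction on pre-operative ESVi, is 0.5. With equal pre and post SDs, s = 1 − pre–post correlation, so this is a pre–post correlation of 0.5. The plan introduces 12 as the SD of ESVi ("we expect the standard deviation of LV end-systolic volume indexed to body surface area (ESVi) will be 12 ml/m^2") and then uses it for change. Since SD of change = 12 × √(2(1 − ρ)), the two uses agree only at ρ = 0.5.

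**Step 1: the plan's own figure.** A two-sided t-test with 48 per group, a difference of 7 and SD 12 has power 0.807, and the minimum detectable difference is 6.93 ml/m². The plan's figure reproduces.

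**Step 2: effect of a baseline imbalance.** A median split on ECV gives a difference in mean pre-operative ESVi of D = 2√(2/π) × r × 12 = 1.596 × r × 12. The raw contrast is then 7 − s × D. Example at r = 0.3: D = 1.596 × 0.3 × 12 = 5.74; s × D = 2.87; contrast = 7 − 2.87 = 4.13.

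| r | D | s × D | Raw contrast (true 7) | t-test power | t-test rejections if ECV has no effect |
|---|---|---|---|---|---|
| 0 | 0 | 0 | 7.0 | 81% | 5% |
| 0.2 | 3.83 | 1.91 | 5.1 | 54% | 12% |
| 0.3 | 5.74 | 2.87 | 4.1 | 39% | 21% |
| 0.4 | 7.66 | 3.83 | 3.2 | 25% | 34% |

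The excess rejections in the last column point away from the hypothesis (a larger reduction with high ECV).

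**Step 3: same data, adjusted for pre-operative ESVi.** Simulation with n = 96 under this model gives an adjusted estimate of about 7 throughout. Power is about 90% at r = 0, 88% at r = 0.3 and 87% at r = 0.4.

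**Step 4: range.** A milder case (r = 0.2, s = 0.3) gives 5.85 ml/m² and 66% power. A stronger one (r = 0.4, s = 0.7) gives 1.64 ml/m² and 10%. The sign reverses only if 1.596 × 12 × r × s > 7, that is r × s > 0.37, for example r = 0.6 with s = 0.7.

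**Step 5: the opposite model.** Suppose instead that the gap D is stable, so each half keeps its own mean apart from the effect of surgery, with a within-group pre–post correlation of 0.5. The raw change contrast is then unbiased and rejects a null effect about 5% of the time. The adjusted contrast is off by (1 − 0.5) × D = 1.9, 2.9 and 3.8 ml/m² at r = 0.2, 0.3 and 0.4, in favour of the hypothesis. It rejects a null effect in about 14%, 26% and 40% of simulated trials.

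**The case against.** Four objections carry weight.

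- **The t-test stands only in the Power calculation.** A reader might infer that the trial has committed itself to an unadjusted primary analysis. The documents do not support that. Sizing on a t-test and analysing with covariates is common, and a statistical analysis plan that is not shown may name covariates. What stands is that the article describes no other analysis of the primary comparison and rests its power on this one.
- **The imbalance is not documented.** A reader might infer that high-ECV patients must start with larger ventricles. The Abstract ties fibrosis to strain and volume overload, not to ESVi. The pilot correlations are with strain and exercise capacity only. The link is plausible, but its size is an assumption.
- **Adjustment is not always right.** For pre-existing groups this is Lord's paradox, and Step 5 shows the adjusted estimate biased where the raw one is not. The Discussion also places fibrosis upstream of ventricular dysfunction, so pre-operative ESVi may partly mediate the ECV effect. This objection stands. It is the reason to report both contrasts and to state the estimand.
- **Reversal of a true effect.** A reader might infer it from the direction of the bias. It needs r × s above about 0.37, the far end of any reasonable range, so it should not be presented as likely.

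**Conclusion.** The concern holds in a limited form. As described in the article, the primary comparison is a raw change contrast between non-randomised halves, with no account taken of pre-operative ESVi. If ECV correlates with pre-operative ESVi at 0.2 to 0.4 and the pre–post correlation is 0.5, a true 7 ml/m² deficit shrinks to about 5.1 to 3.2 ml/m², and power falls from about 80% to between 54% and 25%. These figures depend on the two assumed correlations and on a model in which ventricles of equal starting size share the same expected recovery apart from ECV.

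The case for adjustment does not rest on the imbalance alone. The Discussion's aim of a marker independent of chamber volume calls for the ECV difference at a given starting volume. Under the same model, adjustment raises power from about 80% to 90% even with no imbalance.

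**What to change.** State the primary analysis as a linear model of 9-month ESVi on ECV group, with pre-operative ESVi as a covariate and a short prespecified set already collected, such as age and sex. Using change as the outcome gives the same ECV coefficient apart from sign. State the estimand as the difference between ECV groups at a given pre-operative ESVi, with its 95% CI.

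Report the unadjusted change contrast beside it as a prespecified sensitivity analysis, and say in advance that the two answer different questions and may disagree.

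Do not add regurgitant volume by default. The section on cardiac magnetic resonance imaging derives it from LV stroke volume, which itself contains end-systolic volume, so it is coupled to the ESVi covariate.

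If an unshown analysis plan already adjusts in this way, a sentence saying so is enough.

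The cost is wording. No visit, measurement or recruitment target changes, and the planned 96 patients suffice. Some precision is lost if ECV and ESVi are correlated: the variance inflation from pre-operative ESVi is 1/(1 − (2/π) × r²), or 1.03 at r = 0.2 and 1.11 at r = 0.4. Further covariates may add a little.

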### Monitoring and safety assessments

Interventions in this study will be carried out according to the decision of the clinician responsible for the patient and are therefore independent of the study itself. Therefore, there is no formal data monitoring committee.

## Discussion

Physicians and patients with asymptomatic severe primary degenerative MR are faced with a significant conundrum. Delaying surgery until the onset of a class I surgical indication is associated with a possible outcome penalty for the patient [43]. Yet it is also difficult to advocate early surgery in the asymptomatic, elderly patient, when watchful-waiting offers a reasonable probability of remaining symptom-free for potentially the remainder of the patient’s life without penalty if an operation becomes necessary [11]. There is a clear unmet need for objective and quantitative markers of LV disease that can contribute to the decision regarding the optimal time for MV surgery.

The Mitral FINDER study aims to identify why patients with the same severity of MR can have such wide-range of symptoms before, and difference in ventricular response after surgery. By improving our understanding of ventricular remodelling in MR, and establishing the relationship between myocardial fibrosis and early ventricular dysfunction, this study will offer physicians a novel non-invasive biomarker that can further inform the timing of surgery. Measuring myocardial T1 relaxation offers a quantitative method of assessing ventricular fibrosis in primary MR that is not dependent on chamber volume and is not therefore subject to the limitations of ejection fraction in volume overload. This non-invasively measured imaging biomarker of fibrosis will be validated on myocardial biopsy performed at the time of MV repair. It is central to the hypothesis that patients with more myocardial fibrosis are at risk of sub-clinical myocardial dysfunction, followed by subjective exercise intolerance, that ultimately leads to overt cardiac dysfunction and irreversible myocardial damage that manifests as impaired reverse LV remodelling. We propose that in a population of patients with severe primary degenerative MR, without a class I indication for surgery, the presence of interstitial fibrosis as assessed by higher myocardial T1 / ECV values will identify patients with an increased risk of LV dysfunction after surgery. If this is shown, then there may be a role for routine use of CMR to risk stratify patients who would truly benefit from “early” surgery. It would also provide a rationale for larger clinical trials designed to examine cardiovascular morbidity and mortality end-points, as well as the use of anti-fibrotic treatments such as spironolactone to reverse or delay LV fibrosis in asymptomatic severe MR.

## Abbreviations

ACC: American College of Cardiology
AHA: American Heart Association
AoSV: aortic stroke volume
AT: anaerobic threshold
CMR: cardiac magnetic resonance
CPET: cardiopulmonary exercise test
ECG: electrocardiogram
ECV: extracellular volume
EF: ejection fraction
EHVG: Elastic Van Gieson
ESC: European Society of Cardiology
FT: feature tracking
Gd: gadolinium
Hct: haematocrit
HLA: horizontal long axis
HRV: heart rate variability
IABP: intra-aortic balloon pump
ITU: intensive therapy unit
LA: left atrium
LV: left ventricle
LVESVi: left ventricular end systolic volume index
LVOT: left ventricular outflow tract
LVSV: left ventricular stroke volume
MLWHF: Minnesota Living with Heart Failure
MR: mitral regurgitation
MRV: mitral regurgitant volume
MV: mitral valve
NYHA: New York Heart Association
RF: regurgitant fraction
SA-ECG: signal-averaged electrocardiogram
SSFP: steady-state free precession
VCO2: carbon dioxide production
VLA: vertical long axis
VO2: oxygen consumption
